### Study participants

All trauma patients who present to the ED will be invited to participate. The specific inclusion criteria are: patients who speak Chinese; aged ≥ 18 years; report moderate to severe intensity of acute pain upon admission (defined as a pain score ≥ 4 according to the Numerical Rating Scale [NRS]); are able to take deep breaths to use the self-managed device; are willing to participate in the study and sign informed consent. Patients are ineligible if they have considered contraindications to using the premixed gas (intracranial hypertension, recent ophthalmic surgery, epilepsy, unconsciousness, pneumothorax / hemothorax, facial traumas, intestinal obstruction, pulmonary embolism, emphysema, sinusitis, and retinal detachment [17]). Other exclusion criteria are: recent receipt of analgesics within 6 h; life-threatening situations or instability of clinical vital signs; pregnancy; individuals in police custody; or individuals included in another study.

All participating clinicians will be associate chief physicians, will have worked in the ED for > 5 years, and will be willing to participate in and receive training from the originator who conceived and designed the protocol. In this trial, two fixed clinicians who meet all the above criteria will be included.

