### Measurement

The investigator will record participants’ characteristics, demographic data (age, sex, nationality, weight, and height), and physiological parameters (pulse rate, blood pressure, and oxygen saturation). Other information regarding pain score, diagnosis of traumatic injury, total length of gas inhalation, analgesic prescription, adverse effects, satisfaction of patients and healthcare professionals, as well as the acceptance from patients will be recorded by the researcher.

Self-assessment of pain severity will be measured with the NRS. The NRS is a tool with great reliability and validity that is frequently used for assessing pain level from zero (painfree) to ten (worst pain intolerable) [31]. The physical parameters will be monitored via an electronic manometer (OMRON, HEM-7120) and OXIMETER (PC-60B). The evaluated pain score along with non-invasive monitoring of blood pressure, heart rate, and digital monitoring of oxygen saturation at baseline (T0) before the intervention, 5 min (T1), and 15 min (T2) after the beginning of the intervention, and at 5 min (T3) after the intervention.

Any observed adverse effects of the fixed nitrous oxide/oxygen mixture and oxygen will be carefully evaluated and recorded by the investigator after the beginning of the gas administration. The prospectively occurred adverse effects include gastrointestinal adverse effects (vomiting, nausea), respiratory adverse effects (oxygen desaturation which defined as pulse oximetric saturation ≦ 94%, arterial hypotension, and bradycardia), and any other discomfort (numbness, dizziness, drowsiness, oversedation, and headache) [32]. If any adverse effects take place, patients will be given inhaled oxygen and in < 5 min the adverse effects will vanish. All severe adverse effects and management of them during the gas inhalation will also be noted.

Both patients’ and healthcare providers’ satisfaction with pain administration under the new analgesia will be investigated by a five-point satisfaction scale (5, very satisfied; 4, satisfied; 3, uncertain; 2, dissatisfied; 1, very dissatisfied) [33]. Moreover, the acceptance will be obtained by asking patients whether they would accept the same gas inhalation in case of another trauma with moderate to severe pain (yes / no). The satisfaction and the acceptance are recorded at T3.

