### Outcome measures

#### Primary outcome measure

The primary outcome measure will be the level of pain relief after the initiation of the intervention, which is assessed and recorded by the data collector according to the pain level provided by patients using a self-assessment scale (NRS).

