### Sample size determination

Based on our previous studies on cancer breakthrough pain and burn-dressing pain [32, 34], this study uses pain severity as the primary endpoint measure for sample size calculation. We used preliminary visits obtained in our ED for 20 patients and calculated the sample size at 5 min (T1) and 15 min (T2) after the beginning of intervention. It is observed that 65% of patients receiving premixed nitrous oxide/oxygen had pain relief at T1 compared with 8% of patients receiving oxygen (a decrease in pain intensity of at least 30% was recommended as the pain relief [35]). We found that 70% of patients in the experimental group experienced pain relief at T2 versus 10% in the control group. It aimed to determine a appropriate target sample size that would provide a 90% power (*β* = 0.10) for two-tailed testing with 5% type-1 error rate of the measure. We separately calculated a minimum requirement of 30 patients or 24 patients for total with the formula [36, 37]. In practice, we finally decided on 90 samples (45 per group) to improve the power of this study.

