### Data analysis

SPSS version 22.0 (Chicago, IL, USA) will be used to conduct the statistic analysis, initially according to the intention-to-treat principle. All patients randomized should be included in the analysis and missing data will be handled using multiple imputation. Descriptive statistics will be adopted to describe the population demographic data by medians (interquartile ranges [IQR]; min–max), means (standard deviations), and proportions (exact binomial 95% confidence intervals [CIs]), as appropriate. The comparison of means will be assessed by Student’s *t* test or non-parametric test and using the Mann–Whitney test to compare means of continuous variables if applicable. Chi-squared tests or Fisher’s exact test will be performed to compare the proportions of categorical variables. The analysis of physiological parameters and scores at baseline, T2, and T3 were performed by analysis of covariant (ANCOVA) adjusting for the respective baseline value on the two groups (“experimental” and “control”). We considered all *P* values < 0.05 to be statistically significant.

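### If relief of at least 30% is compared by the stated unadjusted test for proportions, T0 NRS is left out as a covariate; adding it is a small gain in precision and consistency, not a correction of bias

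*Protocol article*

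**What the plan says.** - **Outcome.** Primary outcome measure: "The primary outcome measure will be the level of pain relief after the initiation of the intervention", self-rated on the NRS. No cut-off is given there.
- **Definition of relief.** Sample size determination is the only place with a rule: "a decrease in pain intensity of at least 30% was recommended as the pain relief". The relief proportions used are 65% versus 8% at T1 and 70% versus 10% at T2.
- **Scale and entry.** The NRS runs from 0 to 10 (Measurement). Entry requires moderate to severe pain, "defined as a pain score ≥ 4 according to" the NRS (Study participants). T0 therefore lies between 4 and 10 and is recorded before the intervention.
- **Proportions.** Data analysis: a chi-squared or Fisher "exact test will be performed to compare the proportions of categorical variables". No covariate is named.
- **Scores.** The same section analyses physiological parameters and scores by ANCOVA, "adjusting for the respective baseline value on the two groups". The time points listed are baseline, T2 and T3; T1 is not among them.
- **Allocation.** 1:1, with no stratification by pain severity stated.

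**The concern.** The plan adjusts scores for baseline but not proportions, and the proportion with relief is what the sample size rests on. A percentage rule appears to take care of baseline because each fall is divided by T0. On whole-number scores it does so only in part. The required fall jumps from 2 to 3 points between T0 6 and T0 7, so a 2-point fall counts as relief in one patient and not in the other. If T0 predicts relief, a chance difference in severity between two arms of 45 adds noise to the relief comparison. A covariate that is already collected could remove some of that noise. What is at stake is a little precision, and having the adjusted analysis fixed before anyone sees whether the arms differ at T0.

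**Working it through.** **1. The plan's own figures.** Two-sided 5%, 90% power, (1.960 + 1.282)² = 10.51.
- T2, 70% v 10%, usual formula (pooled variance under the null, unpooled under the alternative): 12 per arm, total 24, as stated.
- T1, 65% v 8%, pooled variance in both terms: 10.51 × 2 × 0.365 × 0.635 / 0.57² = 14.99, so 15 per arm, total 30, as stated. The usual formula gives 13 per arm, total 26.

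Each figure matches a standard formula, though no single formula tried gives both. Both treat relief as a simple proportion without covariates.

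**2. Fall needed for relief.** Smallest whole k with k/T0 ≥ 0.30. Whole-number scoring is assumed; the article does not state it.

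| T0 | 4 | 5 | 6 | 7 | 8 | 9 | 10 |
|---|---|---|---|---|---|---|---|
| Points | 2 | 2 | 2 | 3 | 3 | 3 | 3 |
| % fall | 50 | 40 | 33.3 | 42.9 | 37.5 | 33.3 | 30 |

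**3. How far relief could depend on T0.** The article gives neither a T0 distribution nor the spread of falls. Assume T0 uniform on 4-10 and overall relief of 65% v 8%.
- Falls proportional to T0 (SD 0.20): treated relief 51-75% across T0, control 4-12%.
- Falls a fixed number of points (SD 1.5): treated 78.5% at T0 4-6 and 54.9% at T0 7-10; control 13.5% and 3.9%.

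**4. Effect of chance imbalance with 45 per arm.** The middle 95% of random T0 mixes gives an expected risk difference of 54.3-59.6 points (proportional) or 53.3-60.7 points (fixed), around a planned 57.

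**5. Share of the variance due to T0.** The unadjusted variance is (0.65 × 0.35 + 0.08 × 0.92)/45 = 0.3011/45, an SD of 8.2 points. With fixed-point falls, 3/7 of patients have T0 4-6 and 4/7 have T0 7-10. The between-T0 part is (3/7)(4/7)(0.236² + 0.096²) = 0.0159, and 0.0159/0.3011 = 5%. The same sum over the seven proportional-fall values gives 0.0081/0.3011 = 3%. These shares are ceilings on what adjustment can remove in these two scenarios. Simulations at 65% v 8% and 70% v 10% gave variance reductions of roughly 1-8% for fixed-point falls and about 0 (-1% to 2%) for proportional falls. The share grows as the spread of falls narrows, so the 5% ceiling for SD 1.5 is not a limit for every spread.

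**6. Validity of the unadjusted test.** The simulated type I error of chi-squared under random allocation was 5.1-6.3% for null rates of 8%, 30% and 65%, highest at the sparse 8%. Power at 45 per arm exceeds 99.9%.

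**7. Sparse data.** Expected control responders at T1: 45 × 0.08 = 3.6. The chance of none is 0.92⁴⁵ = 2.3% at T1 and 0.90⁴⁵ = 0.9% at T2. An ordinary logistic fit then has no finite arm coefficient.

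**The case against.** **The premise is inferred.** No sentence says that the 30% proportion is the analysed endpoint or names its test. The sentence on proportions is generic and would also cover acceptance and adverse events. This stands, and the point has to be worded conditionally. The inference is still reasonable, because this is the only method the article offers for a proportion.

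**T0 is already used.** The 30% rule is relative to T0, and scores at T2 and T3 get a baseline-adjusted ANCOVA. This also stands. What is missing is T0 as a covariate in the comparison of proportions. At T1, which the ANCOVA list omits, no baseline-adjusted analysis is stated.

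**Covariates belong in the SAP, which is not shown.** This would dispose of a complaint about silence. Here the article states a method for proportions and a different principle for scores, so the suggestion improves on stated text. It does not report an omission.

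**A reader might infer that the relief result is biased by the T0 mix of the arms.** The documents do not support that. Allocation is random, and chance imbalance is already part of the unadjusted standard error. A striking example can mislead: if relief were 68% at T0 4-6 and 42% at T0 7-10 (mean fall 2.2 points, SD 1.5), 10 extra severe patients in one arm would move the difference by 10/45 × 0.26 = 5.8 points. But 10/45 is 22 points of share. With half the patients severe, the SD of that imbalance is √(2 × 0.25/45) = 10.5 points, so this is about a 2.1 SD event. A 1 SD imbalance moves the difference by 0.105 × 0.26 = 2.7 points. Those relief rates also match neither planned arm.

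**The change is not free of risk.** With so few control responders expected, a plain logistic model can fail. This stands, and the fix needs a fallback.

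**Conclusion.** The point holds as a minor improvement. The threshold arithmetic is right for whole-number scores, and the stated test for proportions leaves out a baseline value that the plan uses for scores. The unadjusted comparison remains valid. The gain is a variance reduction of about 0-8% in the risk difference, near zero if falls are proportional to T0, and the conclusion at the planned effect would not change. These sizes rest on assumed whole-number scoring, T0 distribution and fall models, and on reading the generic sentence on proportions as covering the 30% rule. The practical value lies mainly in treating scores and relief alike and in ruling out a later choice between adjusted and unadjusted results.

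**What to change.** Keep the 30% definition. In Data analysis, state that relief is compared with a logistic model containing arm and T0 NRS, with the form in which T0 enters fixed in advance. Report the standardised risk difference with its 95% CI. Retain Fisher's exact test as the supporting analysis. Name it also as the fallback, or name a Firth-penalised fit instead, for when an arm has zero or very few responders, and give the number that triggers the switch. Date the change before unblinding.

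The cost is analysis wording and a short standardisation step. T0 NRS is already collected, and neither the sample size nor trial conduct changes.

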**Methods:**

The randomized, double-blind, prospective, placebo-controlled study will be carried out in the Emergency Department of General Hospital of Ningxia Medical University. The target research objects are trauma patients who present to the Emergency Department and report moderate to severe intensities of acute pain. A total of 90 patients will be recruited and randomly assigned into the treatment and control group. The treatment group will receive conventional pain treatment plus nitrous oxide/oxygen mixture and the control group will receive conventional pain treatment plus oxygen. Neither patients, nor investigators, nor data collectors will know the nature of the gas mixture in each cylinder and the randomization list. Outcomes will be monitored at baseline(T0), 5 min (T1), and 15 min (T2) after the beginning of intervention and at 5 min post intervention (T3) for each group. The primary outcome is the level of pain relief after the initial administering of the intervention at T1, T2, and T3. Secondary outcomes include adverse events, physiological parameters, total time of the gas administration, satisfaction from both patients and healthcare professionals, and the acceptance of patients.

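### The baseline-adjusted ANCOVA is listed at baseline, T2 and T3: it leaves out T1, a primary time point, and names the covariate as an outcome

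*Protocol article*

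**What the plan says.** All references are to the protocol article.

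- **Measurement.** Pain score, blood pressure, heart rate and oxygen saturation are taken "at baseline (T0) before the intervention, 5 min (T1), and 15 min (T2) after the beginning of the intervention, and at 5 min (T3"), the last counted from the end of gas inhalation, which makes four occasions.
- **Abstract, Methods.** "The primary outcome is the level of pain relief after the initial administering of the intervention at T1, T2, and T3".
- **Primary outcome measure.** "The primary outcome measure will be the level of pain relief after the initiation of the intervention", scored on the NRS. This section names no time point, so the abstract is where the primary times are given.
- **Sample size determination.** The investigators "calculated the sample size at 5 min (T1) and 15 min (T2) after the beginning of intervention". The planning rates are "65% of patients receiving premixed nitrous oxide/oxygen had pain relief at T1 compared with 8% of patients receiving oxygen" and "70% of patients in the experimental group experienced pain relief at T2 versus 10% in the control group", with relief defined as a fall in pain intensity of at least 30%.
- **Data analysis.** "The analysis of physiological parameters and scores at baseline, T2, and T3 were performed by analysis of covariant (ANCOVA"). The same sentence then describes the model as "adjusting for the respective baseline value on the two groups". The section also provides t or Mann–Whitney tests for continuous variables and chi-squared or Fisher tests for proportions. Neither pair is tied to a time point.

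**The concern.** The ANCOVA sentence is the only one in Data analysis that ties a method to time points, and its list does not match the rest of the article. T1 is absent. The Background gives an onset of no more than 2 min, so 5 min is the first scheduled look at both effect and vital signs. Baseline is listed among the analysed time points, yet the same sentence makes it the covariate.

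The stake is consistency and pre-specification. As printed, one measure (the NRS score) is analysed with baseline adjustment at two of its three primary times and without it at the third. The vital signs, which serve the safety objective, are treated in the same uneven way. An analyst must either follow a list that disagrees with the primary outcome or depart from the published plan. That leaves the choice between an adjusted and an unadjusted T1 result open until the data are in hand.

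**Working it through.** The plan states no figure on this point that could be reproduced. The check is a comparison of the sections, followed by two short calculations.

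**1. Time points side by side**

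| Section | T0 | T1 | T2 | T3 |
|---|---|---|---|---|
| Measurement | yes | yes | yes | yes |
| Primary outcome (abstract) | – | yes | yes | yes |
| Sample size determination | – | yes | yes | – |
| ANCOVA, as outcome (Data analysis) | yes | **no** | yes | yes |
| ANCOVA, as covariate (Data analysis) | yes | – | – | – |

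T1 is the only post-baseline time without an ANCOVA, and T0 is the only entry in both ANCOVA rows.

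**2. Baseline as outcome and covariate**

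The model as written would be T0 = a + b × group + c × T0 + error. Least squares gives a = 0, b = 0, c = 1 and a residual sum of squares of 0, whatever the data. The F test for group is then 0/0. A fit to simulated NRS scores (4 to 10, 45 per arm) confirmed this to rounding error: group coefficient −4e-15, baseline coefficient 1.000, residual sum of squares 4e-27. Baseline therefore cannot be meant as an outcome.

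**3. Possible readings of the sentence**

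- *Baseline* is a slip for T1. The list becomes T1, T2, T3 and agrees with the abstract. The missing T1 and the misplaced baseline are then one wrong word.
- *Baseline* is listed only because its values enter as covariate. The empty model disappears, but T1 is still missing.

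Neither reading of the printed words gives T1 an ANCOVA.

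**4. Precision lost on T1 means**

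Let r be the within-group correlation between the T0 and T1 values. With a linear relation and 1:1 randomization,

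variance (unadjusted difference) / variance (ANCOVA difference) = 1 / (1 − r²).

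The article gives no r, so a range is assumed. The last column is 90 × (1 − r²), the number of patients who would give the same precision under ANCOVA as all 90 give unadjusted.

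| r (assumed) | 1 − r² | Variance ratio | 90 × (1 − r²) |
|---|---|---|---|
| 0.3 | 0.91 | 1.10 | 81.9 |
| 0.5 | 0.75 | 1.33 | 67.5 |
| 0.7 | 0.51 | 1.96 | 45.9 |

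These ratios apply to means of NRS scores or vital signs. They do not apply to a responder proportion.

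**5. The responder comparison at T1**

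The planning rates are 65% and 8%, with 45 per arm and two-sided 5%. The pooled proportion is (0.65 + 0.08)/2 = 0.365.

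- SE under the null: √(2 × 0.365 × 0.635 / 45) = 0.1015.
- SE under the alternative: √((0.65 × 0.35 + 0.08 × 0.92) / 45) = 0.0818.
- z = (0.57 − 1.96 × 0.1015) / 0.0818 ≈ 4.5, so power exceeds 99.9%.

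The T2 rates (70% and 10%) also give power above 99.9%. The error in the ANCOVA list does not touch this comparison.

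**The case against.** The strongest reply is that this is an editorial slip with little consequence. The sentence itself identifies baseline as the covariate, and no analyst would regress T0 on T0. If one did, the output would be visibly empty and could not mislead. The endpoint on which the trial was sized is a responder proportion. Its natural test is chi-squared or Fisher, which the plan offers without limiting it to any time point. A 30% fall is measured from the patient's own starting score, so that comparison already uses baseline. For means, an unadjusted comparison in a randomized trial is valid and gives up only precision. Vital signs are secondary, are still recorded at T1, and can be compared there by t or Mann–Whitney tests.

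Most of this stands, and it limits how far the point can be taken. A reader might infer that the T1 primary outcome is left untested; the article does not support that, because the general tests cover it. A reader might count an omitted time point and an untestable model as two separate failures; on the likeliest reading they are one word. A reader might take the variance ratios as a loss of power for the trial; they rest on assumed correlations and concern means only.

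The reply does not make the printed list right. Even on the kindest reading T1 has no adjusted analysis, and the list contradicts the abstract and the basis of the sample size. Nor is this a detail that an article leaves to a fuller document, because the article states the list explicitly.

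**Conclusion.** The point holds as a misstated list of time points, of moderate severity. That T1 is missing is certain from the text. That *baseline* was written for T1 is probable but cannot be proved from the article.

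Taken literally, the list leaves NRS scores and vital signs at T1 with unadjusted comparisons of means only, out of step with T2 and T3. For r between 0.3 and 0.7 (assumed) this costs a variance 1.10 to 1.96 times that of ANCOVA. No bias follows, the sample size is unaffected, and the responder comparison at T1 remains available with power above 99.9% at the planning rates.

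**What to change.** Replace the ANCOVA sentence in Data analysis with: *NRS scores and physiological parameters at T1, T2 and T3 will be compared between groups by ANCOVA with the baseline (T0) value as covariate.* Present T0 values by group descriptively, without a test.

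This brings the section into line with the abstract, Measurement and Sample size determination. It costs one sentence and needs no new data, because T1 is already recorded. Recruitment has begun, so the correction should be made and dated before the blind is broken; the T1 analysis is then fixed before results by group can be seen.

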### Ethics and dissemination

The findings of this study will be shared with healthcare workers, patients, the general public, and relevant departments through open-access articles, public talks, conferences, and final reports. Any modifications of this protocol and changes to eligibility criteria or outcomes will be communicated with the DMC, clinicians, trial participants, and research ethics committee review board. There are no professional writers to be employed to complete the manuscript. Authorship eligibility guidelines which comply with the International Committee of Medical Journal Editors (ICMJE) guidelines [38] will be adhered to.

